### Sample Size

Sample size for the RCT was based on 80% power to detect a 20% difference in the percentage maintaining an improvement in F&V consumption at 24 months. This sample size also provides 80% power to detect a small-to-medium effect size for differences in mean F&V consumption based on Cohen’s definition [57]. The primary hypothesis was that the treatment groups would maintain their initial gains in F&V consumption better than the control group, and the TLC-GST group would be significantly more successful in achieving this outcome than the TLC-SCT group (ie, GST > SCT > Control). This was tested defining maintenance as sustaining a one-serving increase in F&V that was achieved during the acquisition phase (as this is the eligibility criterion for the RCT). This primary hypothesis was tested using two approaches: a categorical approach and a continuous approach. The categorical hypothesis tests the proportion of the group who maintain, while the continuous tests the differences in F&V serving size. For the categorical hypothesis, the sample size estimation was based on a 20% difference in the proportion of participants meeting the definition of maintenance between groups. If the proportion maintaining gains is 80% in one group, 60% in another, and 40% in a third, there is 80% power of detecting pairwise differences between groups. Expecting 5% attrition at every 6 months from baseline to 24-month time point, a sample size of 405 (n=135 per group) is required at baseline and will yield a final sample of 330 (n=110 per group). This sample size provides 81% power of detecting the difference at 24-month time point between TLC-SCT and Control Groups (60% vs 40%), 87% power of detecting the difference between TLC-GST and TLC-SCT Groups (80% vs 60%), and 99% power of detecting the difference between TLC-GST and Control Groups (80% vs 40%), testing at the two-tailed alpha .05 level. For the continuous hypothesis, group differences are measured by the mean change from baseline to 24-month time point. A sample size of 110 provides 80% power of detecting an effect size of .38 of the standard deviation of the change score in F&V servings.

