## Results

### Data Analysis

Data will be analyzed using SAS, version 9.1 for Windows. Alpha level was set at *P*<.05. Descriptive statistics will be used to characterize the different study subject samples before and after the acquisition study period. Descriptive statistics will examine those individuals who were screened for eligibility and those who qualified and enrolled into the RCT. Sample comparisons between those who were eligible and those who were not will be made using data collected at enrollment (screening data). Comparisons of the different study samples will be performed using Student’s *t* test for continuous variables and Pearson’s chi-square test for categorical variables. An additional analysis will be performed evaluating the change in F&V servings from initial screening (enrollment) to baseline (ie, the beginning of the maintenance phase) for the sample who was randomized into the RCT. An intention-to-treat approach using the last observation carried forward approach will be used to include those participants who drop out of the study or for whom there are missing data.

The primary hypotheses for the RCT is that the treatment groups will maintain their initial gains (ie, one-serving increase) in F&V consumption better than the control group, and the TLC-GST group will be significantly more successful in achieving this outcome than the TLC-SCT group (ie, GST > SCT > Control) on both a categorical (primary hypothesis) and a continuous measure (secondary hypothesis) of maintenance at all follow-up time points. The primary time points for the study will be baseline (randomization), 6 months (post intervention period), and 24 months (end of the follow-up period). The primary comparisons will be considered from baseline to 6 months, and baseline to 24 months. Group differences will be compared using a continuous variable (F&V consumption) at these time points. We will also compare groups on the percent who maintained a one-serving/day or greater increase in F&V consumption. The categorical measure of maintenance will be analyzed through multiple logistic regression models, and a continuous measure of maintenance will be analyzed through multiple linear regression models. Independent variables in these models will include a set of indicator variables for study group, baseline levels relating to each outcome variable, and potential confounders (variables found to differ between groups at baseline).

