Longitudinal models will be used to explore group differences on dietary indicators over time, using data from all study evaluation points. These analyses will use the Generalized Estimating Equations (GEE) approach to accounting for the longitudinal nature of the data by modeling the within-subject correlation and adjusting both regression parameters and standard errors for this correlation. As compared to traditional repeated measures analysis of variance, the GEE approach allows for the inclusion of all available data from subjects with incomplete follow-up in the analysis. For categorical outcome measures, GEE logistic regression models for longitudinal data will be used, while for continuous outcome measures, GEE linear regression models will be used. Independent variables in these models will include a set of indicator variables for group, a set of indicator variables representing time (with baseline taken as the reference group), and a set of interaction terms modeling differential changes over time for the three study groups. Potential confounders identified in preliminary analyses will also be included in these models. Our primary interest is in the interaction terms, which will test whether the pattern of change in consumption of F&V over time differs by group.

While the primary focus of our analyses of the number of F&V servings is on changes from baseline to 6 to 24 months, our longitudinal models will also allow us to examine maintenance decay in the number of servings from 6 months (at the end of the maintenance intervention) to 24 months. Similarly, our longitudinal models for the categorized maintenance outcome will allow us to examine changes in maintenance from 6 to 24 months as well.

Secondary analyses will examine the influence of psychosocial variables. For TLC-SCT, we hypothesize that the outcomes are mediated by self-efficacy. For TLC-GST, we hypothesize that outcomes are at least partially explained by changes in goal system variables such as levels of inter-goal facilitation, inter-goal substitution, and inter-goal conflict at all major follow-up time points.

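### The exploratory GEE linear model for F&V servings makes no use of baseline as a covariate, so its baseline-referenced group-by-time terms are change-score contrasts that give up some precision

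*Protocol article*

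**What the plan says.** The Data Analysis section of the protocol article describes two sets of between-arm models.

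- **Visit-specific regressions**, logistic for the categorical measure of maintenance and linear for the continuous one. These carry the baseline-to-6-month and baseline-to-24-month comparisons and adjust for baseline: "Independent variables in these models will include a set of indicator variables for study group, baseline levels relating to each outcome variable".
- **Longitudinal GEE models**, introduced as a way to explore group differences over all evaluation points. Their terms are group indicators, "a set of indicator variables representing time (with baseline taken as the reference group), and a set of interaction terms modeling differential changes over time". Baseline level is not among the listed covariates. Of these models the article says: "Our primary interest is in the interaction terms, which will test whether the pattern of change in consumption of F&V over time differs by group".

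The Sample Size section sizes the continuous hypothesis on the change score: "group differences are measured by the mean change from baseline to 24-month time point". It adds: "A sample size of 110 provides 80% power of detecting an effect size of .38 of the standard deviation of the change score in F&V". On attrition it says "Expecting 5% attrition at every 6 months from baseline to 24-month time point", and that "a sample size of 405 (n=135 per group) is required at baseline and will yield a final sample of 330 (n=110 per group").

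**The concern.** Baseline can be the reference level of time only if the baseline measurement is itself one of the outcomes. With group indicators also in the model, each arm then has its own freely estimated baseline mean. An interaction of group with a follow-up visit is the arm difference at that visit minus the arm difference at baseline, which is the contrast of raw change scores.

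Participants are randomised at baseline, so the true baseline means are equal by design. Estimating them separately adds baseline sampling noise to every contrast that is referenced to baseline.

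Two things follow for the linear model of servings. Its 6-month and 24-month contrasts are less precise than they need be. The report will also carry two different estimates of the same comparison, one adjusted for baseline and one not, and these can disagree. This matters because the GEE model is the only between-arm model described that uses every visit, and the one meant to show the pattern over time.

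**Working it through.** **Inputs from the Sample Size section.** 135 per arm randomised; 5% attrition per 6 months; 110 per arm at 24 months; effect .38 SD of the change score; two-sided alpha .05. Attrition check: 135 × 0.95^4 = 109.96.

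**Assumed, because the plan does not give them.** The correlation rho between baseline and follow-up F&V (.3, .5 and .7 are shown); equal SDs at baseline and follow-up; exchangeable correlation across visits; dropout completely at random.

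**Step 1: reproduce the plan's figure.** z = .38 / √(2/110) = 2.82. Power = Φ(2.82 − 1.96) = 80.5% (80.1% from the noncentral t). The stated 80% is correct for the change score.

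**Step 2: confirm what the interaction estimates.** A GEE with group, time and group-by-time was fitted to one simulated complete data set (110 per arm, five visits). The 24-month interaction was 0.30441 and the difference in mean change was 0.30441. The standard error was 0.12661 both ways. This held under independence and exchangeable working correlation.

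**Step 3: cost with complete data.** With a common SD σ, the change score has variance 2σ²(1 − rho) and the baseline-adjusted outcome has σ²(1 − rho²). The ratio is (1 + rho)/2, so adjusted z = 2.82 / √((1 + rho)/2).

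| rho | variance ratio | change score | adjusted | gain (points) |
|---|---|---|---|---|
| .3 | .65 | 80.5% | 93.8% | 13.3 |
| .5 | .75 | 80.5% | 90.2% | 9.8 |
| .7 | .85 | 80.5% | 86.4% | 5.9 |
| .8 | .90 | 80.5% | 84.4% | 3.9 |
| .9 | .95 | 80.5% | 82.4% | 2.0 |

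**Step 4: cost under the planned attrition.** The GEE model is meant to use incomplete follow-up, so this is the more relevant case. Large-sample variances for 135 per arm, 5% dropout per visit and all available data give:

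| rho | free group term | shared baseline mean | loss (points) |
|---|---|---|---|
| .3 | 83.3% | 94.0% | 10.7 |
| .5 | 82.9% | 90.8% | 7.9 |
| .7 | 82.6% | 87.4% | 4.8 |

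A simulation of 250 trials per rho agreed within its error: 82.8%, 84.0% and 81.6% against 93.6%, 89.2% and 85.6%.

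**Step 5: sensitivity to equal SDs.** With complete data, and a follow-up SD of 0.8 to 1.25 times the baseline SD, the gain over rho .3 to .7 runs from 0.8 to 17.4 points.

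**Step 6: the decay contrast.** The 6-to-24-month contrast is the difference of two interactions: (Y24 − Y0) − (Y6 − Y0) = Y24 − Y6. Baseline cancels. Under exchangeable correlation the variance with and without the group main effect is the same (ratio 1.000 at rho .3, .5 and .7, with complete data and with 5% dropout per visit). Only a correlation that falls with time would bring a gain; a first-order autoregressive pattern reduces the variance by about 4 to 16%.

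**Step 7: a caution on the remedy.** If the group main effect is dropped but the working correlation is independence, the 24-month term is simply the difference in 24-month means, with no baseline adjustment. At rho .7 the effect is .38 × √(2 × .3) = .294 follow-up SDs, so z = .294 / √(2/110) = 2.18 and power = Φ(2.18 − 1.96) = 59%. That is worse than the model as written.

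**The case against.** The strongest reply is that nothing planned is lost. The longitudinal models are introduced as exploratory, and the baseline-to-6-month and baseline-to-24-month comparisons belong to regressions that already adjust for baseline. The continuous hypothesis was sized on the change score, and the GEE model delivers that power: 80.5% with complete data and about 83% with the planned attrition. Group, time and group-by-time is a standard, valid and unbiased specification. All of this stands, and it limits the point to a refinement of one exploratory model.

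Some stronger readings are tempting, and the document does not support them.

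- A reader might infer from "Our primary interest is in the interaction terms, which will test whether the pattern of change in consumption of F&V over time differs by group" that the trial's main comparison is affected. That sentence names the terms of interest within the longitudinal models, not the primary analysis.
- A reader might take the complete-data gain of 6 to 13 points as the size of the loss. It needs complete data, rho between .3 and .7 and equal SDs. The plan expects attrition and states neither rho nor the SDs. Entrants are selected for low intake and then for an increase, so equal SDs cannot be taken for granted.
- A reader might suppose that every contrast from the model suffers, including decay. Step 6 shows that it does not under exchangeable correlation.
- A reader might attribute any disagreement between the two sets of models to baseline adjustment alone. They also differ in data: the article announces last observation carried forward as its general approach to dropout, while the GEE models use what was observed.

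The structural diagnosis survives. The stated terms do leave baseline unadjusted in the linear GEE model, and randomisation makes the adjustment available at no cost.

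**Conclusion.** The point holds as a modest loss of precision in the exploratory GEE linear model for F&V servings. It is not bias, does not concern the GEE logistic model, leaves the baseline-adjusted regressions untouched and undercuts no stated power figure.

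Under the plan's attrition and .38 SD effect, with equal SDs and exchangeable correlation, the 24-month contrast has about 83% power against about 94%, 91% and 87% for a baseline-adjusted model at assumed rho .3, .5 and .7. The loss is about 5 to 11 points. It shrinks at higher rho and moves with the ratio of follow-up to baseline SD. With dropout and a non-independence working correlation, the interactions are only approximately raw change-score contrasts. The adjustment is worth making because it is free, not because the plan fails without it.

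**What to change.** Reword the GEE linear model for F&V servings so that the outcomes are the follow-up visits only (6, 12, 18 and 24 months). Its terms would be group, time, group-by-time, baseline F&V and baseline-by-time. Test the 6-month and 24-month group contrasts from that model. They then target the same baseline-adjusted comparison as the visit-specific regressions.

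An alternative is to keep baseline as an outcome and drop the group main effects, so that the arms share one baseline mean. The plan must then also state a non-independence working correlation, such as unstructured or exchangeable. Under independence this version does not adjust for baseline and can lose power (Step 7). It relies on equal true baseline means, which randomisation provides.

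The cost is one sentence of analysis wording. It needs no new data and no change to the sample size.

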## Methods

### Overview

The design for this study includes two phases to examine the maintenance of a dietary behavior change in adults. Figure 1 provides an overview of the study flow and measurement time points. In the first phase (acquisition), an intervention was used to produce a change in F&V consumption in order to study, in a second phase (maintenance), if an intervention targeting maintenance could sustain that change. All interventions were delivered using a fully automated telephony system that used an interactive voice response (IVR) system to generate speech that emulated counseling by a trained behavioral counselor combined with a speech recognition system to understand what the participant said. To perform the study, a sample of healthy adults who consumed less than the recommended level of F&V (ie, ≤ 5 servings/day) were recruited. During the acquisition phase, they were given a tested dietary telephony intervention for up to 6 months, called Telephone-Linked Care (TLC)-EAT, which has been shown in previous studies to have positive effects on initiating dietary improvements, including increased F&V consumption [32,33]. Because both prior studies found an increase of approximately one serving of F&V for the TLC-EAT intervention group, it was hypothesized that this effect would occur in a new sample of participants. F&V intake was examined at enrollment and after 3 months of the acquisition intervention. Participants who increased their consumption of F&V by at least one serving/day became eligible for the second phase (maintenance). Participants who did not show a one-serving increase were allowed to participate for an additional 3 months only. Those who achieved a one-serving increase during the acquisition study were eligible to participate in the second phase (maintenance, randomized controlled trial). Participants who entered the second (maintenance) phase of the study were blinded to the inclusion criterion (eg, an increase of >1 serving/day of F&V). Participants in the maintenance phase were randomized to one of three groups, receiving one of two theoretically based TLC interventions targeting maintenance of behavior (TLC-Maintenance GST or TLC-Maintenance SCT) or to the control group (an assessment only without an intervention). All participants in the randomized controlled trial (RCT) were assessed every 6 months for a total of 2 years post randomization (baseline). The study protocol received full board review and approval by the Boston University School of Medicine Institutional Review Board (NCT00148525). See Multimedia Appendix 1 for the CONSORT-EHEALTH checklist [34].

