### Procedures

The University of Rhode Island Survey Research Center performed study recruitment, assessment, and randomization. The Center randomly selected names from a voter registration list and mailed a letter inviting them to participate in the study. The letter was followed by a phone call from the Center about one week later where the interviewer described the study, screened for eligibility (see Participant section above for eligibility criteria), obtained verbal consent, and administered study instruments. Research assistants at Boston University School of Medicine, where the intervention (ie, TLC-EAT) was hosted, sent participants an enrollment packet in the mail, which contained a welcome letter, consent form for their records, and a manual and personal password for the healthy eating acquisition intervention (ie, TLC-EAT). A week after enrollment, these research assistants called participants to train them on how to use TLC-EAT. Participants did a practice call with the research assistant on the line. Those who completed the training were transferred to the first intervention call (the “training call”) with TLC-EAT. Thereafter, all TLC calls were outbound calls initiated by the automated system, which called participants at the time initially entered into the automated scheduling system during the training call. Participants were asked to complete one TLC-EAT call per week for 12 weeks with the option of rescheduling any of the incoming TLC calls or initiating calls to TLC if preferred. After 12 weeks, F&V consumption was reassessed with the NCI FVS to determine eligibility for the maintenance phase of the trial. Participants who increased by one serving of fruit and/or vegetable were eligible to be randomized to one of three groups for the RCT. Random allocation to group assignment was generated by the SRC’s computer program that used urn randomization protocols to balance groups by gender. Those who did not increase by one serving after 3 months were invited to continue with the acquisition intervention, TLC-EAT, for an additional 3 months and then were assessed again for eligibility into the RCT. Those who qualified and agreed to continue in the RCT were assessed at baseline (randomization), 6, 12, 18 and 24 months post baseline. A random sample of those who qualified for the RCT were invited to complete a blood draw at the university’s General Clinical Research Center at baseline only. Assessments during the RCT included the NCI FVS, 24-hour dietary recalls, and psychosocial measures. Participants received US $20 for completing a survey at baseline, 6-month, 12-month, 18-month, and 24-month time points, and $50 for the in-person, fasting blood draw.

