#### Fruit and Vegetable Intake

The primary outcome measure was F&V, and it was assessed two ways: brief screeners and 24-hour dietary recalls. The NCI FVS [35] was considered the primary screener and was administered at all assessment time points. The screener assesses self-reported frequency of consumption in the last month and the portion size for 10 items that included 100% fruit juice, fruit, lettuce salad, french fries or fried potatoes, white potatoes (not fried), cooked dried beans, other vegetables, tomato sauce, vegetable soup, and mixtures that include vegetables. Although all questions were asked, fried potato consumption and mixtures that include vegetables were not included in the summary scores or analyses. Validity of the FVS compared to true intake ranges from *r*=.66 for men to *r*=.51 for women [35].

For the primary assessment time points for the RCT (baseline, 6, and 24 months), the primary assessment of F&V was the NCI Method [54,55]. This method requires a food frequency assessment such as the NCI FVS and two 24-hour dietary recalls. The recalls were administered over the telephone by the Nutrition Epidemiology core at University of North Carolina, Chapel Hill, using the latest version of the Nutrition Data System for Research (NDSR) software. A nutritionist trained to conduct the telephone recalls used a standard introduction script and a multiple-pass approach interview methodology for the recall. The foods, beverages, preparation methods, amounts, and recipes reported by the participant were entered by an interviewer into the NDSR software to obtain an estimate of nutrient intake. The NDSR 2008 database was used for this study and contained over 18,000 foods, 8000 brand name products, many ethnic foods, supplements, and vitamins. The NDSR calculated food group serving count system was used to assess F&V.

Maintenance of F&V consumption was defined in this study as sustaining a one-serving/day increase in F&V achieved during the acquisition phase. Participants who increased their consumption by more than one serving during the acquisition phase need only maintain a one-serving gain to be considered as achieving maintenance. Maintenance (sustaining at least one serving/day) will be assessed at each time point, separately.

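### The exploratory GEE logistic model for binary maintenance takes baseline as its reference time, but on the qualifying screener everyone is a maintainer at baseline, so its group-by-time terms cannot be estimated

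*Protocol article*

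**What the plan says.** **Entry rule.** Overview: "Participants who increased their consumption of F&V by at least one serving/day became eligible for the second phase (maintenance". Procedures names the instrument: "After 12 weeks, F&V consumption was reassessed with the NCI FVS to determine eligibility for the maintenance phase of the trial". Those who missed the gain could continue for 3 more months and were then reassessed.

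**Outcome.** Fruit and Vegetable Intake: "Maintenance of F&V consumption was defined in this study as sustaining a one-serving/day increase in F&V achieved during the acquisition phase". Sample Size says why that threshold was chosen: "as this is the eligibility criterion for the RCT". The NCI screener "was considered the primary screener and was administered at all assessment time points". The NCI Method, which adds two 24-hour recalls, is the primary assessment at baseline, 6 and 24 months only.

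**Model.** Data Analysis introduces longitudinal models over all evaluation points to explore group differences. "For categorical outcome measures, GEE logistic regression models for longitudinal data will be used", with linear GEE for continuous outcomes. One description of the covariates serves both: group indicators, "a set of indicator variables representing time (with baseline taken as the reference group"), and their interactions. It adds: "Our primary interest is in the interaction terms". The same section says that the longitudinal models of categorised maintenance will be used to look at change from 6 to 24 months. Nothing sets a different reference time, or a different set of visits, for the binary outcome.

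**The concern.** The outcome threshold and the entry threshold are the same. At randomisation the binary indicator therefore equals 1 for everyone if it is computed from the assessment that qualified them. A logistic model that takes this visit as its reference measures every change against an infinite log-odds. Baseline reference coding suits the servings outcome, but it does not carry over to the maintenance indicator.

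At stake is the only longitudinal model that the article describes for binary maintenance. Run as written, it gives no usable test of whether the arms lose maintenance at different rates. Some software reports convergence with arbitrary coefficients, so the failure may not be noticed.

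**Working it through.** **1. The plan's own figures.** Sample Size gives 405 at baseline (135 per arm), 5% attrition per 6 months, 330 (110 per arm) at 24 months, and assumed maintenance of 80% (GST), 60% (SCT) and 40% (control).
- Attrition: 405 × 0.95^4 = 329.9, as stated.
- Power, with continuity correction and n = 110: Φ{[(d − 1/n)√n − 1.96√(2p̄(1−p̄))] / √(p1(1−p1) + p2(1−p2))}, where d = p1 − p2 and p̄ is their mean. This gives 81.3% (60 v 40), 87.6% (80 v 60) and over 99.9% (80 v 40). The article states 81%, 87% and 99%.

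These inputs are sound and are used below.

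**2. The interaction as specified.** With group, time and group-by-time terms and baseline as reference, the GST-control term at 24 months is

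[logit(GST, 24) − logit(GST, 0)] − [logit(control, 24) − logit(control, 0)].

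With 135/135 maintainers at baseline in each arm, both baseline logits are +∞. The expression is [logit 0.8 − ∞] − [logit 0.4 − ∞], which is undefined. The same holds for all eight interactions (two arms by four visits).

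**3. What software returns.** I simulated three trials of 135 per arm and five visits, with no dropout. Baseline was 100% and the 24-month rates were the article's. The 6-, 12- and 18-month rates are my assumptions (control 60/53/46%, SCT 75/70/65%, GST 90/87/83%), as is a latent within-person correlation of 0.5.
- Independence working correlation: intercepts 28.5 to 28.6. The standard error of the 24-month GST-control interaction was not computable in one trial and about 33,400 and 34,700 in the others.
- Exchangeable: intercepts 33.8 and 35.8 in two trials and no fit in the third. The interaction standard error was not computable in any.

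**4. The 6-to-24-month contrast.** The infinite term cancels in the difference of two interactions. Under independence the GST-control contrast was −1.07 (SE 0.39), −0.39 (0.44) and −0.03 (0.31). Fits without baseline gave the same values. Under exchangeable the point estimates matched in two trials, but the standard error was 26.9 in one and not computable in the other. The third trial gave no fit.

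**5. If baseline were below 100%.** Let b be the baseline proportion, equal in all arms. Treating visits as independent,

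variance = 2/(135·b(1−b)) + 1/(110·0.8·0.2) + 1/(110·0.4·0.6).

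The last two terms sum to 0.0947, so the direct 24-month GST-control contrast has SE 0.31. Its log odds ratio is logit 0.8 − logit 0.4 = 1.79. The chance that a given arm has no non-maintainer at baseline is b^135.

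| b | SE of interaction | 1.79/SE | b^135 |
|---|---|---|---|
| 85% | 0.46 | 3.9 | under 0.001 |
| 95% | 0.64 | 2.8 | 0.001 |
| 99% | 1.26 | 1.4 | 0.26 |
| 99.5% | 1.75 | 1.0 | 0.51 |

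At 99%, at least one of three arms has no non-maintainer with probability 1 − (1 − 0.257)³ = 0.59, so separation is likely even then.

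**The case against.** The strongest reply is that a baseline of exactly 100% is an assumption. The baseline screener might be a fresh administration, or baseline might be scored by the NCI Method, and then some participants would fall short. This stands as a condition on the point. At about 95% the interaction is finite, with 1.79/SE near 2.8, so it would be wrong to call the model unusable at any baseline close to 100%. But the article describes no separate qualifying and baseline screener. It describes recalls for baseline, 6 and 24 months, not for enrolment, 12 or 18 months. Only the screener gives a like-for-like gain at every visit that the model uses. The alternative criterion in Principal Considerations (intake at the end of acquisition minus a standard error) is also met by everyone at baseline on that scoring.

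Four stronger readings are tempting and not supported:
- **The primary test fails.** It does not. Data Analysis tests the categorical primary hypothesis by multiple logistic regression, and Fruit and Vegetable Intake says each time point is assessed separately. Those models have no baseline row in the outcome. The longitudinal models are exploratory, and the stated primary interest refers to terms within them.
- **The servings model fails too.** It does not. Baseline reference is sound for the linear GEE.
- **The 6-to-24-month comparison is lost.** It is recoverable in principle (step 4). The risk is numerical and depends on a working correlation that the article does not fix.
- **The baseline covariate in the separate logistic models is a constant.** That holds only if the baseline level means the binary indicator. Baseline servings is at least as natural a reading, and a constant would leave the arm estimates unchanged.

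It may also be said that visit coding belongs in a fuller plan. That would excuse silence, but the article states a reference time and applies it to both kinds of outcome.

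**Conclusion.** The point holds, limited to the exploratory GEE logistic model for binary maintenance. With baseline scored on the qualifying screener, which is the only like-for-like scoring that the article supports, every participant in every arm is a maintainer at the reference time. None of the eight group-by-time terms can then be estimated, whatever the true effect. That result is algebra; the simulations only show how it appears in output. If baseline were re-measured, the terms would be estimable but imprecise at about 95%, where the variance is 0.407/0.0947, or about 4.3 times that of the direct 24-month contrast. At about 99% the ratio is 1.591/0.0947, or about 17, and the terms are again unusable. The primary categorical analysis and the linear model for servings stand. This should be corrected, but it does not threaten the trial's main conclusion.

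**What to change.** For binary maintenance, state that the GEE logistic model is fitted to the 6-, 12-, 18- and 24-month visits only, with 6 months as the reference time. Report arm contrasts at 6 and 24 months, and use group-by-time as the test of differential decay. Adjust for continuous baseline servings, not the binary indicator. Keep baseline as the reference time only for the continuous outcome.

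Fitted this way to the data of step 3, the model converged in all three trials under both working correlations. The standard error of the 24-month GST-control interaction was 0.31 to 0.44. The cost is one sentence of analysis text, with no new data and no change in sample size.
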